# THE PROPOSED TRIAL

## What is the proposed trial design?

A two arm, cluster randomized trial of the effect of playground surface on playground injury rates will be performed. 37 Schools have been randomized, 19 to receive a wood fibre (Fibar®) playground surface and 18 to receive a granite sand playground surface. Playground injuries will be recorded prospectively for two school years following the intervention.

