### Primary Outcome Measure

Based on OSBIE data from 1999-2001 we estimate a baseline arm fracture (lambda zero) rate of 4 per 1000 student years. A clinically significant difference would be a halving of this rate to 2 per 1000 student years (lambda one). This is consistent with reports of sand having ½ to 1/6 the injury rate of other surfaces (14). Each school of 410 students provides 820 student years (y) of data over the two year study. Hayes’ method of sample size estimation for cluster randomization was used (25), where the number of clusters (c) per arm is:

Setting alpha = .05 and power at 80%,and k (coefficient of variation between clusters) at 0.2, we estimate that 17 clusters per arm or 34 schools in total will be required. 37 have been randomized so the study should have ample power. Ample power exists if the coefficient of variation is between 0.1 and 0.3 (see appendix).

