## Will the trial address any economic issues?

A cost-benefit analysis will be conducted from the Ontario provincial government perspective since both direct health care costs and education funding fall under the jurisdiction of the provincial government.

Direct health care costs will be calculated from OHIP perspective as follows: a) no visit – no cost. b) physician office visit only – GP minor assessment fee. c) emergency department visit – visit cost for ‘average’ Ontario ED visit according to ICD-10 procedure code assigned. d) inpatient admission – hospital cost for average Ontario hospital according to ICD-10 procedure code assigned. Data for the latter two categories will be obtained from the Ontario Case Costing Initiative ([www.occp.com](http://www.occp.com/)). If necessary, Hospital for Sick Children case costs per ICD-10 code will be used for uncommon diagnoses or procedures. Repeat hospitalizations and emergency department visits will be included. Followup clinic visits will be costed at a GP or specialist minor assessment fee as appropriate. Indirect and out-of-pocket costs will not be not included.

The cost of each surfacing will be based on itemized materials and labour contracts from playground suppliers plus labour costs paid by the Toronto District School Board and associated with installation. Maintenance costs will include annual costs of labour and supplies and will be provided yearly by the TDSB.

A decision analysis model will be used to compare the costs and outcomes of the two surfaces. Injury probabilities assigned to each surface will be based on injury rates observed in the trial. All costs will be expressed in 2004 Canadian dollars. A 10-year time horizon will be used. All costs beyond one year will be discounted at 3%. If one surface results in a better outcome at a lower cost, then the incremental cost savings in direct medical resource utilization per injury prevented will be reported. If one surface results in a better outcome at a higher cost, then the incremental cost per injury prevented will be calculated. Sensitivity analysis will be used to test the robustness of the result to variations in the underlying assumptions. The probability of health outcomes, cost of medical care for each health outcome, cost of intervention, and effectiveness of intervention will be varied over a clinically appropriate range using one-way sensitivity analysis.

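### The cost per injury prevented is chosen from observed rates and tested only one input at a time, so the trial's own sampling error and clustering never reach the economic result

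*Protocol*

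**What the plan says.** The section *Will the trial address any economic issues?* bases each surface's injury probabilities on the rates seen in the trial. Two reporting rules follow. If the surface with the better outcome is also cheaper, medical savings per injury prevented are reported. The second rule reads: "If one surface results in a better outcome at a higher cost, then the incremental cost per injury prevented will be calculated". No rule covers rates that differ by no more than chance.

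Robustness is addressed by one method. Outcome probabilities, medical costs, intervention cost and effectiveness are to be "varied over a clinically appropriate range using one-way sensitivity analysis". The section does not define that range or link it to the trial's confidence interval. It mentions no interval for the ratio, no joint variation of inputs and no allowance for clustering.

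Unit medical costs come from fee schedules and case-costing averages. Surfacing costs come from contracts and school board labour, and maintenance costs from the board.

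**The concern.** Effectiveness is the central input to the model. It is not an external figure with a plausible range but an estimate from 37 schools, with a sampling error that the trial can measure. The section *Give details of the planned analyses* does estimate that error for the primary comparison, with extra variance for clustering. The economic section uses the same rates without carrying the variance forward.

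Two things are at stake. First, a ratio with injuries prevented in the denominator becomes unstable as the rate difference approaches zero. Second, the observed direction decides which surface is called better and which ratio is reported, and that direction can be a chance result. The protocol intends the results for a national standard and for school boards, where a cost per injury prevented would be read as firm.

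**Working it through.** **Inputs.** From the sample size section of the protocol:
- "we estimate a baseline arm fracture (lambda zero) rate of 4 per 1000 student years", with halving to 2 per 1000 as the target
- "Each school of 410 students provides 820 student years (y) of data over the two year study"
- "Setting alpha = .05 and power at 80%,and k (coefficient of variation between clusters) at 0.2"
- "Ample power exists if the coefficient of variation is between 0.1 and 0.3"
- all injuries: 15 per 1000, reduced by 33%

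From the design section: "19 to receive a wood fibre (Fibar®) playground surface and 18 to receive a granite sand playground surface". School sizes and resurfacing costs are from Table 1.

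**Step 1: reproduce the plan's figures.** The unmatched Hayes–Bennett formula is

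c = 1 + (1.96 + 0.84)² × [(λ0 + λ1)/y + k²(λ0² + λ1²)] / (λ0 − λ1)²

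- Fractures, two-sided alpha: 1 + 7.85 × [0.006/820 + 0.04 × 0.00002] / 0.000004 = 16.93, so 17 per arm, as stated.
- All injuries, 15 v 10.05 per 1000: 14.96, so 15 per arm, as stated.

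The same variance model can therefore be used below.

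**Step 2: precision of the fracture rate difference.** With equal school sizes,

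SE = √[λ0/(19 × 820) + λ1/(18 × 820) + k²λ0²/19 + k²λ1²/18]

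- At 4 v 2 per 1000 and k = 0.2, SE = 0.66 per 1000, with about 62 and 30 expected fractures.
- 95% interval: 2.0 ± 1.96 × 0.66 = 0.71 to 3.29 per 1000.
- Upper limit over lower limit: 4.65. It is 4.3 at k = 0.1 and 5.3 at k = 0.3.

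Table 1 shows unequal school sizes. The between-school terms are then multiplied by 1 + (SD/mean)², which is 1 + (312.1/409.2)² = 1.58 for Fibar and 1 + (195.4/416.3)² = 1.22 for sand. With 818 and 833 student-years per school, SE = 0.674, the interval is 0.68 to 3.32 and the spread is 4.9-fold.

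**Step 3: all injuries.** At 15 v 10 per 1000, k = 0.2 and equal sizes, the difference is 5.0 with interval 2.0 to 8.0. The spread is 4.0-fold (3.2 at k = 0.1, 5.7 at k = 0.3).

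**Step 4: a smaller true effect.** At 4 v 3 fractures per 1000, SE = 0.72 and the interval is −0.40 to 2.40. It includes zero, so cost divided by fractures prevented has no finite bound. The observed direction would be wrong with probability Φ(−1.0/0.72), about 8%.

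**Step 5: where the spread reaches the reported ratio.** Let E be injuries prevented, S the extra surfacing and maintenance cost, and m the average medical cost per injury. Assume a similar injury mix in both arms.
- Safer surface dearer: with incremental cost taken net of medical savings, the ratio is (S − mE)/E = S/E − m. The S/E term carries the whole spread in E.
- Safer surface cheaper: medical savings per injury prevented are mE/E = m. The spread largely cancels, but the ratio looks equally stable when E is only noise.

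**The case against.** **Some range will be shown.** Effectiveness and outcome probabilities are among the inputs to be varied. A reader might infer that the result will carry no range at all, and the text does not support that. It also does not exclude varying effectiveness over the trial's confidence interval, which would show the spread computed above. What stands is that nothing ties the range to that interval, and one-way variation cannot show joint error in injuries and costs.

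**The rules are conditional.** The section does not say that a chance difference counts as a better outcome, and the main analysis will report a cluster-adjusted comparison. But the economic section gives no criterion other than the observed result.

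**A dollar spread is tempting but does not follow.** A reader might divide the Table 1 resurfacing gap, $7,073.68 − $5,688.90 = $1,384.78, by 410 pupils × 10 years × the rate difference and obtain $498 down to $102 per fracture prevented. With 4 per 1000 on Fibar and 2 on sand, as in the Table 1 calculation above, sand is both safer and cheaper to resurface. On that cost the plan would report medical savings per injury, and no such ratio arises. The dollar range needs Fibar, the dearer surface in Table 1, to prove safer. It also ignores maintenance, medical costs and discounting.

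**The trial does not supply all costs.** Unit medical costs are external, and resampling schools cannot capture their error. The trial contributes rates and health-care use, and Table 1 shows that surfacing costs vary by school.

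**An analysis plan could add this.** That is possible, and health economists are available to the trial. Still, the protocol names a specific method, and it is the weaker one.

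**Conclusion.** The point holds as a minor improvement to an ancillary analysis. The protocol picks and reports its economic ratio from observed directions and tests it by one-way variation with no stated link to sampling error or clustering.

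The size is a spread in injuries prevented: about 4.7- to 4.9-fold for fractures and about 4-fold for all injuries. These figures assume that the planned effects are true, that k = 0.2 and that a normal-approximation interval is adequate. They describe the denominator, so the spread of the final ratio will differ. The consequence is greatest if the safer surface is also dearer, and for the statement of which surface is better. Maintenance and medical costs are not given, so which rule will apply is unknown.

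**What to change.** State in the economic section that sampling uncertainty will be handled by a cluster bootstrap. Resample whole schools within arm. In each resample, recompute incremental cost and injuries prevented from trial rates, health-care use and school-level surfacing costs. Report their joint interval and the probability that each surface has fewer injuries and lower cost. Say whether the injuries counted are fractures or all playground injuries. Where the joint interval includes no difference in injuries, present incremental cost and injuries prevented separately instead of relying on the ratio.

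Keep one-way analysis for inputs from outside the trial, such as unit medical costs, and for maintenance costs if the board supplies them only as totals.

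The cost is a little extra programming on data already to be collected, and a less definite economic statement.

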## What is the estimated cost and duration of the trial?

It is estimated that the data collection and analysis will cost a total of $100,734.40 over a two year period. The cost of replacing the playgrounds was $1,691,210, which is the school board’s in kind contribution. This contribution by the school board allows a high quality randomized trial to be conducted with high leverage and very modest cost. See attached budget for further details.

# Details of the Trial Team

## Trial Management

### Timelines

Random allocation of intended surfaces to schools occurred in the spring of 2003. HSC ethics review board approval for the study has already been obtained. School playground replacement began in the summer of 2003 and will be completed at all schools in the spring of 2004. The service life of each playground is estimated at 20 years. Data will be collected during two complete school years once funding is received. Data analysis will occur during the three months following completion of data collection.

### Trial Personnel

#### Research Coordinator (.2 FTE)

The coordinator will manage all aspects of implementation and staffing. She will design the study database and perform the data analysis. She will liaise with school and school board personnel during conduct of the trial. The research coordinator will also assist the dissemination of results in consultation with the principal investigators, including the preparation of manuscripts and scientific abstracts.

#### Research Assistant (.6 FTE)

The research assistant will be responsible for the day to day implementation of the study. This will include contacting the parents by mail and telephone and completing the CHIRPP forms, obtaining and coding health records, contacting the school principals, conducting the site inspections, and data cleaning and data entry.

# Ethical Issues

Hospital for Sick Children ethics review board approval has been obtained. Consent for data collection will be obtained from the schools with full disclosure of the trial design, purpose and outcomes. Schools will subsequently provide trial information to the parents at appropriate parent school meetings. Parents will be contacted first by letter, then by telephone within a week of a playground injury to request more detail regarding the injury and to complete the CHIRPP form. Consent will be obtained by telephone by the research assistant. Parents will be reassured that their participation is voluntary, and that the school and the TDSB will not be informed of their decision to participate. Prior contact by letter minimizes any coercive effect of ‘cold calling’ with a research request. We believe that in this situation, the research team is the best first contact because no member of the research team is providing direct patient care to any of the children in the study. Parents may not want the school to know if they agree to participate. Individual identity will be protected by using a study code in the database. Only the research coordinator will be able to link children to the database.

(2) Brown J. A comparison of injuries on various types of playground equipment. 1997:1-3.

(6) [name] C, Hu X, Wesson DE, Parkin PC. Risk factors for severe injuries associated with falls from playground equipment. Accident; Analysis and Prevention 2000 May;32(3):377-382.

